### Outcomes

Table 1 lists all trial outcome measures and the corresponding abbreviated statistical analysis plan.

**Table 1 tab1:** A list of outcome measures and the corresponding analysis plan.

Outcome measure	Description	Statistical analysis
Primary outcomes (safety)—Phase 1 and 2		
1. Incidence of adverse events (# of observed events/sessions)	Hemodynamic instability Skin irritation Patient condition deterioration Unanticipated adverse events	Data type: Count Data Statistical Test: Fisher’s Exact Test
Primary outcomes (efficacy)—Phase 2		
1. ISNCSCI lower motor scores	Immediate change in scores with acute tSCS Change in scores from baseline to post tSCS	Data Type: Integer Statistical Test: Repeated Measures Analysis of Variance
Secondary outcomes (efficacy)—Phase 1 and 2		
1 ISNCSCI sensory + motor scores	Change in scores from baseline to 7DPI or discharge	Data Type: Integer Statistical Test: Repeated Measures Analysis of Variance
2. Spinally motor evoked potentials (MEPs)	MEP present/elicited (binary measure) (within subject) # of muscles with elicitable MEP	Data Type(s): Binary, Count Statistical Tests: Chi-Square, Fisher’s Exact Test
3. Electromyography (EMG) amplitude	Change in EMG amplitude in the presence of tSCS vs. no stimulation (within subject) Change in number of muscles with EMG output	Data Type(s): Continuous, Count Statistical Tests: Repeated Measures Analysis of Variance, Fisher’s Exact Test
Secondary outcomes (biomarker discovery)—Phase 1 and 2		
1. Neuronal (UCH-L1) and glial cell (GFAP) injury markers in blood	Changes in protein levels from baseline to post tSCS vs. sham	Data Type: Continuous Statistical Tests: Repeated Measures Analysis of Variance
2. CSF proteomics	Changes in protein levels from baseline to post tSCS vs. sham	Data Type: Continuous Statistical Tests: Non-linear Principal Components Analysis, followed by RM-ANOVA on PC scores
Secondary outcomes (patient-reported outcomes)—Phase 1 and 2		
3a. Incidence of neuropathic pain at 6-month follow-up 3b. Severity of neuropathic pain at 6-months follow-up	Modified DN4 questionnaire will be used to assess neuropathic pain at 6-months follow-up in tSCS vs. sham individuals (vs. historical TRACK-SCI participants)	Data Type: Integer, or Binarized at ≤ indicating neuropathic pain Statistical Test: Independent group Student’s *t*-test, or Chi-square

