### Analysis of primary and secondary efficacy outcome measures

For all participants, the primary outcome measure(s) will be: incidence of adverse events (number) for Phase 1 and 2 and change in ISNCSCI lower motor score over time for Phase 2. Secondary outcomes in both phases will be: ISNCSCI sensory scores, AIS grade, peak EMG amplitude, and mean EMG amplitude. For Phase I, change scores will be measured between baseline and post-trial, and in Phase II each measure will be taken across 5 trials. For all repeated measures analyses, we will use a factorial within-subjects repeated-measures analysis of variance (RM-ANOVA) to assess statistically significant change over time. This approach will allow us within a single statistical test to assess (1) the overall between-subjects effect of stimulation to determine the group differences between the stimulation and control groups, (2) the difference in changes over time between groups, and (3) the within-subjects effect of stimulation over trials, to determine the extent to which each individual changes over time. The RM-ANOVA procedure will be run for each outcome measure.

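### The closing RM-ANOVA sentence puts ordinal AIS grade under analysis of variance, and AIS grade has no row in Table 1

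*Protocol article*

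**What the plan says.** In the protocol article, the section on analysis of primary and secondary efficacy outcome measures names two primary outcomes: "incidence of adverse events (number) for Phase 1 and 2", and change in ISNCSCI lower motor score for Phase 2. It then gives the secondary outcomes: "Secondary outcomes in both phases will be: ISNCSCI sensory scores, AIS grade, peak EMG amplitude, and mean EMG amplitude". It says that in Phase 2 each measure is taken at five trials. The method is introduced with a scope: "For all repeated measures analyses, we will use a factorial within-subjects repeated-measures analysis of variance (RM-ANOVA"). The paragraph ends more broadly: "The RM-ANOVA procedure will be run for each outcome measure".

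Table 1, in the Outcomes section, is introduced as covering all trial outcome measures.

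- Adverse events: "Data type: Count Data Statistical Test: Fisher’s Exact Test".
- Lower motor scores, and sensory plus motor scores: RM-ANOVA.
- EMG: "Statistical Tests: Repeated Measures Analysis of Variance, Fisher’s Exact Test", the first for amplitude and the second for the number of muscles.
- Motor evoked potentials: "Data Type(s): Binary, Count Statistical Tests: Chi-Square" and Fisher's exact test.
- AIS grade: no row.

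The patient-reported and biomarker sections set their own tests. A generalized estimating equation is offered as an alternative only for the proteomic components.

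**The concern.** AIS grade has five ordered categories, and entry is restricted to A, B or C. Within a week of injury each participant's series is likely to be flat or to contain a single step. RM-ANOVA treats the letters as equally spaced numbers and takes its error term from within-person scatter around the arm means. With about five people per arm that scatter may be exactly zero, or may come from one or two people.

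The group-by-time test is the one affected. The section relies on it to compare change over time between arms, so it is the treatment comparison for this outcome. If the sentence is followed, a recovery measure that readers will look for is reported either with no test statistic or with a p-value whose error rate is not known in advance.

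The two places also disagree on what the outcomes are. AIS grade is in the analysis section but not in the table said to be complete.

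**Working it through.** **No figure to reproduce.** The Sample size section quotes observed power for motor and sensory scores from a study of 60 people with chronic injury. It gives nothing for AIS grade, and no error rate for RM-ANOVA at this sample size.

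**Inputs from the document.** Phase 2 has 10 participants, planned 5 v 5 (Trial design). Entry is AIS A to C (Eligibility criteria). Phase 2 measures are taken at five trials (analysis section). Alpha is 0.05 (Sample size).

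**Assumptions.** Each participant improves by one grade with probability p during the inpatient window, the same in both arms. The documents do not give p, so 5% to 50% is shown. The number of graded visits k is 2 (Table 1's baseline to 7 days or discharge), 5 (the five trials) or 6 (those plus baseline).

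**Step 1: when F cannot be computed.** If nobody changes grade, the numerator and error sums of squares for time and for group-by-time are both zero. The probability is (1 − p)^10, whatever k is and however the ten split between arms.

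| p | (1 − p)^10 |
|---|---|
| 5% | 0.60 |
| 10% | 0.35 |
| 20% | 0.11 |
| 30% | 0.03 |
| 50% | 0.001 |

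The between-group main effect is hardly touched, because people start at different grades. It was undefined in at most 0.5% of simulated trials, and its false-positive rate was 4.4% to 6.2%.

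**Step 2: interaction test, conversions all between the same two visits.** Each person's change is then 0 or 1 and F does not depend on k. With a and b converters among 5 per arm, F = (a/5 − b/5)² / [s²(1/5 + 1/5)], where s² is the pooled variance of the 0/1 changes. Only the critical value depends on k: 5.318 on (1, 8) df for k = 2, 2.668 on (4, 32) for k = 5, and 2.449 on (5, 40) for k = 6.

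Take two converters against none. The arm variances are 0.30 and 0, so s² = 0.15 and F = 0.16 / (0.15 × 0.4) = 2.667. That is significant at k = 6, just misses at k = 5, and is far from significant at k = 2. Enumerating all pairs (a, b) with binomial weights gives the false-positive rate among trials where F exists:

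| p | k = 2 | k = 5 | k = 6 |
|---|---|---|---|
| 5% | 0.005 | 0.005 | 0.087 |
| 10% | 0.016 | 0.016 | 0.148 |
| 20% | 0.043 | 0.049 | 0.199 |
| 30% | 0.059 | 0.080 | 0.188 |
| 50% | 0.059 | 0.108 | 0.147 |

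**Step 3: conversions spread over the visits.** Simulation (6,000 null trials per setting, no sphericity correction) gave 0.002 to 0.073 at k = 5 and 0.015 to 0.096 at k = 6.

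**Step 4: sphericity correction.** With Greenhouse-Geisser, the spread pattern gave at most 0.043. In the clustered pattern all within-person change lies along one time contrast. The estimated epsilon is therefore 1/(k − 1), the test is referred to (1, 8) df, and the k = 2 column applies: about 6% at most.

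**Step 5: the alternative.** For Fisher's exact test on improved or not at 5 v 5, only these splits reach two-sided 0.05:

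- 5 v 0: p = 2/252 = 0.008.
- 4 v 0, and its complement 5 v 1: p = 10/210 = 0.048.

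Three against none gives 20/120 = 0.167. The true size is 0.0005, 0.005, 0.012 and 0.022 at p = 10%, 20%, 30% and 50%. If nobody converts, the test returns p = 1. For 0 of 5, the exact 95% interval has upper limit 1 − 0.025^(1/5) = 0.52.

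**The case against.** The strongest reply is that the closing sentence should be read with the one that introduces the method, which confines RM-ANOVA to repeated-measures analyses. A reader might infer that RM-ANOVA is imposed on every outcome in the trial. The document does not support that: patient-reported outcomes have chi-square and t tests, and the biomarkers have their own plan. This stands, but it does not free AIS grade, which the same paragraph lists among measures taken repeatedly.

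A reader might also infer that Table 1 names a different test for AIS grade. It does not; it omits the outcome. The chi-square and Fisher entries belong to evoked potentials and muscle counts, which the analysis section does not list. The only outcome in both places with different tests is adverse-event incidence, and only on the literal reading.

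The third tempting reading is that the F test would generally give too many false positives. That depends on facts the documents do not supply. If few people convert, which is the reason for expecting flat series, the uncorrected test is mostly conservative; the exception is clustered conversions at six visits. A correction that removes most of the inflation may sit in an analysis plan that is not shown. An undefined F leads to no false claim, since the analyst would report that nobody changed.

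Finally, the Sample size section calls efficacy exploratory, and no decision rests on an AIS p-value. That limits the weight of the point.

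**Conclusion.** The point holds in limited form. The protocol assigns RM-ANOVA to an ordinal outcome for which it is poorly suited, offers no alternative for that outcome, and leaves it out of the table said to be complete. The closing sentence is also worded loosely enough to catch adverse-event incidence, against Table 1.

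At 10% to 30% conversion, between roughly one trial in three and one in thirty-five would yield no F for time or interaction. Where F exists, the uncorrected interaction test can be far below or well above its nominal 5%, depending on conversion rate, number of visits and clustering. These sizes rest on assumed conversion rates, equal arms and integer coding. They do not show that the test is generally anti-conservative, and the between-group test is close to nominal. Because AIS grade is secondary and efficacy is exploratory, this is a minor to moderate correction.

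**What to change.** Reword the closing sentence of the analysis section so that RM-ANOVA applies to the repeated score and amplitude outcomes: lower motor, sensory and total ISNCSCI scores, and peak and mean EMG amplitude. State that adverse-event incidence follows Table 1's Fisher test.

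Add an AIS row to Table 1: number improving by at least one grade from baseline to 7 days or discharge, and from baseline to 6 months, by arm in Phase 2, with exact confidence intervals. Fisher's exact test should be labelled supportive only. Phase 1 has a single group, so its count stands alone.

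The cost is one sentence and one table row; both assessment times are already planned. The downside is that Fisher's test at this size is very conservative (true size about 0% to 2%) and has little power. The counts and their wide intervals will carry the information, which suits the stated aim of estimating variability and effect sizes for later trials.

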### Analysis of patient-reported secondary outcome measures

At 6-month follow-up, patient-reported outcome measures will be: neuropathic pain as measured by the DN4, quality of life as measured by the NeuroQoL, and functional independence measured by the SCIM. For DN4 data, incidence (count data) and severity (ordinal) will be assessed by Chi square and independent samples *T* test, respectively. NeuroQoL and SCIM measures will also be analyzed using independent samples *T* test.

### Analysis of biomarker discovery measures

Measures of UCHL-1 and GFAP protein will be taken over time and will be analyzed using repeated measures analysis of variance. To assess the big-data, high-dimensional proteomics from Aim 3, our statistical analysis plan consists of a two-tiered strategy of multivariate feature-extraction on multidimensional endpoints, followed by hypothesis testing for association with stimulation at the multivariate and univariate level. This approach will allow us to maximize power while minimizing N. Feature extraction on these metrics will be performed using non-parametric, non-linear principal component analysis (NL-PCA) followed by hypothesis testing with factorial within-subjects ANOVA, or non-parametric generalized estimating equation (GEE) as appropriate.

### Interim analysis

Prior to initiation of the Phase 2 component, a qualitative interim review of safety data from Phase 1 participants will be performed. This assessment will evaluate the type, frequency, and seriousness of adverse events to identify any emerging safety signals and to confirm that continuation to Phase 2 is appropriate. The results will be reviewed by the Principal Investigator and study team and reported to the IRB and in the quarterly progress reports to the Department of Defense.

## Confidentiality

Personal information of enrolled participants will be collected and maintained in secure, password-protected electronic systems compliant with institutional and HIPAA requirements. Access to identifiable data will be limited to authorized study personnel. Participants will be assigned unique study identification numbers, and identifiable information will be stored separately from research data. Data shared outside the study team, including for analysis or publication, will not contain direct identifiers. Regulatory authorities and the study sponsor may review identifiable records as required for monitoring or audit purposes. All records will be retained in accordance with institutional policy and federal regulations.

## Data sharing

De-identified individual participant data underlying the results reported in this study will be made publicly available through the Open Data Commons for Spinal Cord Injury (ODC-SCI; https://odc-sci.org) following publication of the primary results. Shared materials will include the final dataset, data dictionary, and relevant metadata necessary to reproduce the analyses. Data will be released under a Creative Commons Attribution 4.0 International (CC BY 4.0) license, permitting reuse, distribution, and adaptation with appropriate attribution. The code will be made available via GitHub.

## Dissemination policy

Upon study completion, aggregate study results will be made available through ClinicalTrials.gov, scientific conferences, and peer-reviewed publications. Participants who express interest in receiving study results will be provided with a plain-language summary of the overall study findings once data analysis is complete and results are publicly available. No individual participant results will be disclosed unless clinically indicated.
